#### 2.8.2. Data Management

All data will be stored in a password-protected electronic database and double-checked for accuracy and completeness by a second researcher. Personal identifying information will be stored separately from research data using participant ID codes, and all analyses will be conducted on anonymized datasets. Access to the final dataset will be restricted to principal investigator and authorized research team members. Data will be securely archived for a minimum of five years following study completion, in accordance with applicable institutional and national regulations. Given the low-risk nature of the intervention, no independent data monitoring committee (DMC) has been established.

## 3. Ethics and Dissemination

### 3.1. Auditing

Given the low-risk nature of the intervention and the academic scope of this trial, no independent auditing procedures are planned. The principal investigator will oversee study conduct, ensure adherence to the protocol, and perform periodic internal reviews to monitor data quality and ethical compliance.

### 3.2. Ethics Approval

This study protocol has received ethical approval from the Ethics Committee of the Catholic University of Valencia (reference: UCV/2022-2023/123). The study will be conducted in accordance with the principles of the Declaration of Helsinki and applicable national and international ethical standards.

All interventions will comply with the ethical guidelines of the Official College of Physiotherapists of the Valencian Community (ICOFCV). Prior to enrolment, participants will receive written information about the study objectives, procedures, potential benefits, and risks. Written informed consent will be obtained from all participants before participation.

Participants may withdraw from the study at any time without consequences. Any discontinuation due to AE or clinical deterioration will be documented, and participants will be included in the analysis according to the intention-to-treat principle.

Any important protocol modifications affecting the study design, eligibility criteria, interventions, outcomes, statistical analysis, or administrative aspects will be submitted for approval to the Ethics Committee of the Catholic University of Valencia before implementation and, where applicable, will also be updated in the ClinicalTrials.gov registry.

Personal data will be stored in encrypted files and processed exclusively for research purposes, in compliance with Organic Law 3/2018 on the Protection of Personal Data and Guarantee of Digital Rights.

### 3.3. Consent for Publication

Consent for publication is not applicable, as no identifiable personal data will be published. All results will be reported at the group level.

### 3.4. Dissemination Policy

Study findings will be disseminated through publication in peer-reviewed scientific journals and presentations at national and international conferences. A summary of the main results will be made available to participants upon request. Authorship will comply with ICMJE guidelines, and no professional writers will be involved.

### 3.5. Ancillary and Post-Trial Care

Given the low-risk nature of the intervention, no specific ancillary or post-trial care is planned. In the unlikely event of harm related to study participation, participants will be covered by the institutional insurance of the Catholic University of Valencia, in accordance with Spanish legislation.

### 3.6. Access to Data

Access to the final trial dataset will be restricted to the principal investigator and authorized members of the research team. All data will be anonymized prior to analysis. There are no contractual restrictions on data access.

## 4. Discussion

This study protocol describes a randomized controlled trial designed to evaluate the effectiveness of a multidisciplinary intervention combining PMT, PFM activation, and PSY support in community-dwelling older women with UI and increased fall risk. The intervention aims to improve balance, fear of falling, functional capacity, PFM control, and UI-related symptoms, with greater benefits expected in the most comprehensive intervention arm.

Previous evidence supports the effectiveness of MTP for fall prevention and functional improvement in older adults, as well as the role of exercise-based interventions in the management of UI [86,87,88]. Balance training and progressive strength or power-oriented exercises have been consistently associated with improvements in postural control and mobility. In parallel, PSY approaches addressing fear of falling, emotional regulation, and treatment adherence may enhance the effectiveness and sustainability of physical interventions [89].

In this context, PMT can be considered a specific and optimized form of MTP, incorporating high-velocity resistance exercises to enhance functional performance and fall-related outcomes in older adults. While exercise-based and PFM interventions have demonstrated benefits when applied independently, evidence regarding their combined and integrated application, particularly when supplemented with PSY strategies, remains limited [26,41,90].

This study seeks to address this gap by evaluating a comprehensive, feasible, and scalable intervention model aligned with the objectives of the Decade of Healthy Ageing (2021–2030). By addressing two highly prevalent and interrelated geriatric syndromes, this trial may contribute relevant evidence to inform multidisciplinary prevention strategies in both clinical and community settings.

In addition to its expected clinical benefits, the FIRE-WOMEN intervention may have important implications for healthcare services and public health strategies. By targeting two highly prevalent and interrelated geriatric syndromes, UI and fear of falling, this multidisciplinary approach may contribute to reducing healthcare utilization, preventing disability, delaying dependency, and supporting healthy ageing in the community. If effective, the intervention could represent a feasible model for integrating exercise-based rehabilitation and PSY support within community and primary healthcare settings.

### Limitations

The present protocol has several limitations that should be acknowledged.

(i)The active intervention groups receive substantially more participant–therapist contact than the educational control group (36 supervised exercise sessions vs. four monthly educational sessions), which may contribute to observed between-group differences beyond the specific intervention components. The control condition was intentionally designed to reflect realistic community practice rather than an attention-matched control, and the educational sessions provided to this group, covering healthy ageing, fall prevention, and pelvic floor health, may have improved participants’ knowledge and health-related behaviours, potentially affecting some outcomes, although they were not expected to produce the specific physiological adaptations associated with supervised exercise.(ii)The sample size was calculated exclusively based on the primary endpoint (maximal voluntary contraction pressure assessed by manometric perineometry). Accordingly, this trial may not be adequately powered to detect smaller between-group differences in secondary outcomes or in the pre-specified subgroup analyses according to UI subtype. These analyses should therefore be considered exploratory and hypothesis-generating.(iii)The study is restricted to community-dwelling older women, limiting generalizability to institutionalised populations or men.(iv)Intracavitary EMG amplitudes will be normalised to within-session MVC (%MVC) to reduce inter-session variability; however, this approach does not fully eliminate variability arising from training-induced changes in MVC neuromuscular characteristics, and longitudinal iEMG findings should be interpreted with appropriate caution.(v)Movement velocity during power training sessions will not be directly monitored; although the maximum intended velocity instruction and RPE-based intensity targets provide operational control of the training stimulus, confirmation that participants trained within the intended velocity range on a repetition-by-repetition basis is not possible.(vi)Falls and near-falls will not be prospectively recorded during the intervention or follow-up period; future trials in this population should be adequately powered to include fall incidence as a primary endpoint alongside functional and psychological outcomes.(vii)The a priori sample size was estimated using a repeated-measures ANOVA approximation in G*Power 3.1 [43], as dedicated LMM-specific power calculators are not readily available; under the assumed compound-symmetry covariance structure this approximation is considered conservative and reproducible, but represents a minor methodological limitation of the a priori calculation.

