#### 2.6.1. Adherence and Intervention Fidelity

Adherence will be promoted through regular participant contact (telephone and/or in person), flexible scheduling, and reminder messages prior to assessments. Attendance of ≥80% of scheduled sessions will be considered adequate adherence. Attendance, progression variables (e.g., elastic-band resistance and grip width), and any adverse events (AE) will be recorded throughout the intervention. Reasons for discontinuation will be documented, and outcome data will be collected at each assessment time point whenever feasible, in accordance with the intention-to-treat principle.

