#### 2.6.11. Follow-Up and Co-Interventions

During the 6-month follow-up period, no supervised intervention sessions will be provided. Control participants will be offered access to the intervention components only after completion of the final follow-up assessment. Participants from all groups will be instructed to maintain their usual lifestyle habits, and self-reported physical activity levels will be monitored throughout the follow-up period. In addition, any co-interventions potentially affecting study outcomes, including physiotherapy treatments, PFM rehabilitation, or changes in UI related medication, will be recorded and considered during data interpretation.

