AE will be recorded prospectively using a standardized monitoring log completed by the supervising physiotherapist at the end of each session. AE will be defined as any unintended sign, symptom, or condition occurring during or within 48 h of a session, regardless of causal attribution to the intervention. These will include musculoskeletal complaints (e.g., joint pain, muscle strain), cardiovascular symptoms (e.g., dizziness, chest discomfort, unusual dyspnea), PF-related symptoms (e.g., increased urinary leakage or pelvic pain following exercise), and any fall or near-fall event occurring within the study context. AE will be classified by severity (mild, moderate, severe) and by relationship to the intervention (unrelated, possibly related, probably related, definitely related). Serious adverse events (SAE) will be reported immediately to the principal investigator and to the Ethics Committee of the Catholic University of Valencia in accordance with applicable regulatory requirements. Participants experiencing an SAE will be temporarily or permanently withdrawn from the intervention at the discretion of the supervising clinician and will continue to be included in the intention-to-treat analysis wherever feasible. Participants who are temporarily withdrawn may resume participation once symptoms have resolved and, when clinically indicated, after reassessment by the supervising physiotherapist and medical clearance.

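### Section 2.7.3 logs falls and near-falls prospectively as adverse events, but limitation (vi) says they will not be prospectively recorded; even the log would give counts that cannot be compared between arms

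*Protocol article*

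**What the plan says.** Section 2.7.3 (Adherence, Safety and Co-Interventions) sets up the safety record: "AE will be recorded prospectively using a standardized monitoring log completed by the supervising physiotherapist at the end of each session". An adverse event is "any unintended sign, symptom, or condition occurring during or within 48 h of a session, regardless of causal attribution to the intervention", and the listed examples include "any fall or near-fall event occurring within the study context". Section 2.6.1 agrees that "any adverse events (AE) will be recorded throughout the intervention".

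Item (vi) of the Limitations says: "Falls and near-falls will not be prospectively recorded during the intervention or follow-up period". It makes no exception for the adverse event log. The rest of the item recommends that future trials be powered for fall incidence as a primary endpoint.

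Three further statements bear on how much the log could capture:

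- Item (i) of the Limitations gives the contact per arm as "36 supervised exercise sessions vs. four monthly educational sessions".
- Section 2.6.11 says: "During the 6-month follow-up period, no supervised intervention sessions will be provided".
- The self-report log in Section 2.7.3, completed by participants at T1 and T2, asks about co-interventions only.

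Section 2.7 lists no fall count among the outcomes. The fall-related outcomes are the Short FES-I and the balance tests.

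**The concern.** Both statements name falls and near-falls, both concern prospective recording, and both cover the intervention period. A reader of the article cannot tell whether a fall during a session will appear in the safety results.

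The Discussion describes the participants as "community-dwelling older women with UI and increased fall risk". The programme takes women aged 60 to 80 through single-leg stance with eyes closed, unstable surfaces and reactive stepping (Tables 3 and 8), so a fall is an obvious harm to look for. There is no data monitoring committee (Section 2.8.2) and no independent auditing (Section 3.1). The session log is therefore the main safety instrument described, and its content should not be in doubt.

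Fear of falling is a secondary outcome and enters H4, and the Introduction links it strongly to previous falls. Knowing who fell would help in reading the Short FES-I results.

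**Working it through.** No figure in the plan depends on this point, so there is nothing to reproduce. The check has two parts.

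**1. The two statements side by side**

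| | Section 2.7.3 | Limitations (vi) |
|---|---|---|
| Events | Falls and near-falls within the study context | Falls and near-falls |
| Prospective recording | Yes, at the end of each session | No |
| Period | Sessions and the 48 h after each | Intervention and follow-up |
| Exception stated | None | None |

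They collide wherever the Section 2.7.3 window applies, which is within the intervention period. In the follow-up there is no training or educational session to open a window, so there they do not conflict.

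**2. What the log would cover if Section 2.7.3 is followed**

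Inputs from the document: 18 weeks of intervention; 36 exercise sessions in each exercise arm; 4 educational sessions in control; a window of 48 h (2 days) after each session; 30 women per arm, so 90 in the exercise arms and 30 in control.

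Assumptions: windows do not overlap, every session is attended, and the control group's educational sessions count as sessions. Overlap or missed sessions would lower the coverage, so these are upper bounds. Familiarization and assessment visits are left out.

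- Intervention days: 18 × 7 = 126.
- Exercise arms: 36 × 2 = 72 days; 72/126 = 57%.
- Control: 4 × 2 = 8 days; 8/126 = 6%. If educational sessions do not count, 0%.
- Follow-up, week 18 to week 44: no supervised sessions, so 0 days in every arm.

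If the six psychoeducation sessions in EXVERBPSY also opened windows, that arm could gain up to 6 × 2 = 12 days: 84/126 = 67%. The three exercise arms would then differ among themselves as well.

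The ratio of exercise to control coverage is 72/8 = 9. With the same true fall rate in every arm, the exercise arms could log up to nine times as many falls per woman as control, simply through longer observation.

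The person-time on which the two statements can actually conflict is at most (90 × 72 + 30 × 8)/365.25 = 6,720/365.25 = 18.4 person-years. The whole trial, 120 women over 44 weeks, is 120 × 44/52 = 101.5 person-years.

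**The case against.** The best defence is that the two statements address different things. Section 2.7.3 is operational text about session-linked safety events. Item (vi) is a limitation, and its second half, on fall incidence as a primary endpoint, suggests that its subject is falls as an outcome. A limitation in a discussion does not instruct staff, so it is unlikely that anyone would leave an in-session fall off the log because of it. This is probably what the authors meant, but it is not what (vi) says. The sentence has no qualifier and names near-falls, which Section 2.7.3 lists as a safety item. On the charitable reading, (vi) still needs rewording.

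It can also be said that not collecting fall incidence is a disclosed choice of scope. That stands: the choice is not an error, and the added question is a cheap improvement rather than the repair of a broken outcome. The full protocol and the supplementary assessment schedule are not shown, so the absence of another source of fall data can be stated only for this article.

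Several stronger readings are tempting and are not supported:

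- A reader might infer that the trial's main result is compromised. It is not: the single primary endpoint is maximal pelvic floor muscle strength, and fall incidence is not a planned outcome.
- A reader might count every fall in the community over 44 weeks as lost through the contradiction. The document gives no fall rate, and the statements conflict over at most 18.4 of about 101.5 person-years. Most falls lie outside the log's window whichever statement is followed.
- A reader might expect the two venues to record differently. Nothing suggests this: one standardized log is described.
- A reader might conclude that the Short FES-I comparison needs fall history. The randomized comparison between arms stands without it; falls are useful context only.

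**Conclusion.** The contradiction is real and rests on the wording alone. Section 2.7.3 and Limitations (vi) must be reconciled. The consequence is limited to safety reporting and to context for the fear-of-falling results.

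The second part of the finding is that resolving the conflict in favour of Section 2.7.3 would still not give falls data that can be compared between arms. Coverage is at most 57% of intervention days in the exercise arms and 6% in control, with none from the session-free follow-up. These are upper bounds under the assumptions stated above. The imbalance itself does not depend on them, because it follows from 36 sessions against 4. Without a note on exposure, raw fall counts by arm could make exercise look more harmful than it is.

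This should be corrected before results are reported, but it does not threaten the trial's main conclusion.

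**What to change.** 1. Keep falls and near-falls as logged adverse events as in Section 2.7.3, and state for which arms and over which period the log runs.
2. Reword Limitations (vi) to say that fall incidence is not an outcome and that the trial is not powered for it.
3. Add one item to the self-report log that all four arms already complete at T1 and T2: number of falls, and any injury from them, since the last assessment. Report it descriptively by arm, as safety data and as context for the Short FES-I.
4. Present falls from the session log separately, with the number of sessions or contact time in each arm, so that they are not read as comparative rates.

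The cost is one reworded sentence and one or two items on an existing form. If data collection has begun, the form change needs the ethics submission that Section 3.2 describes for important modifications. The downside is that recall over 18 weeks, and then about six months, undercounts falls. The undercount need not be equal across arms, because participants are not blinded and contact differs widely, so the comparison should stay descriptive.

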
## 5. Conclusions

This study describes the FIRE-WOMEN trial, a four-arm additive randomized controlled trial designed to evaluate whether progressively adding PFM activation instructions and PSY support to a PMT programme provides additional benefits for PFM function, UI severity, balance performance, fear of falling, and physical function in community-dwelling older women.

The trial addresses two highly prevalent and interrelated geriatric syndromes through a multidisciplinary intervention that integrates physical, behavioural, and PSY components within a single rehabilitation programme. By incorporating a rigorous methodology, blinded outcome assessment, long-term follow-up, and a comprehensive evaluation of PF, functional, and psychosocial outcomes, this protocol aims to generate high-quality evidence on the effectiveness of this multidisciplinary intervention and its additive components.

The findings of the FIRE-WOMEN trial may contribute to the development of more comprehensive, evidence-based rehabilitation strategies for older women with UI and may support the implementation of multidimensional interventions aimed at improving PFM function, UI severity, balance performance, fear of falling, and quality of life.

## Figures and Tables

**Figure 1 healthcare-14-02467-f001:**
[figure not shown]
Anticipated participant flow throughout the study, including screening, randomization, allocation, follow-up, and analysis. Abbreviations: PMT: power-based multicomponent training; PFM: pelvic floor muscle; PSY: psychoeducational intervention; Ex: exercise group; ExVerb: exercise plus verbal pelvic floor muscle activation instructions; ExVerbPsy: exercise plus verbal pelvic floor muscle activation instructions and psychoeducation.

**Figure 2 healthcare-14-02467-f002:**
[figure not shown]
Balance exercises.

**Figure 3 healthcare-14-02467-f003:**
[figure not shown]
Power-strength exercises.

**Figure 4 healthcare-14-02467-f004:**
[figure not shown]
Strength exercises.

**Figure 5 healthcare-14-02467-f005:**
[figure not shown]
Aerobic and coordination exercises.

**Figure 6 healthcare-14-02467-f006:**
[figure not shown]
Flexibility exercises.

**Figure 7 healthcare-14-02467-f007:**
[figure not shown]
Experimental design. Abbreviations: PMT: power-based multicomponent training; PFM: pelvic floor muscle; PSY: psychoeducational intervention; EX: exercise; i: initial; f: final; s: seconds; min: minutes; CC: contractions; DUR: duration; INT: intensity; REP: repetitions; RPE: rating of perceived exertion; SES: sessions; SET: sets. Note: Component durations are approximate and may vary slightly across sessions. Recovery periods between sets and exercises are included within the planned total session duration of approximately 55–60 min.

**Table 1 healthcare-14-02467-t001:** Inclusion and exclusion criteria.

Inclusion Criteria	Exclusion Criteria
Women aged 60 to 80 years. Community-dwelling (non-institutionalized). Present UI after clinical diagnosis. Ability to walk independently, with or without assistive devices. Functional independence, defined as a Barthel Index score >90. Preserved cognitive function (MMSE score ≥25; GDS score ≥2 only if MMSE cannot be administered). Willingness to participate throughout the intervention and follow-up periods, with written informed consent provided. Not currently engaged in structured physical exercise programs within the previous 3 months Commitment to attend at least 80% of the scheduled intervention sessions.	Previous diagnosis of: (a) neurological disorders (e.g., Parkinson’s disease, stroke, Alzheimer’s disease); (b) severe musculoskeletal conditions limiting physical activity; (c) unstable cardiovascular disease (e.g., unstable angina, NYHA class III-IV heart failure), that could interfere with intervention or assessments. Surgery involving the PF, spine, hip, or knee points within the previous 6 months. Presence of pelvic organ prolapse grade II–IV. Current or recent (<3 months) participation in other structured exercise or intervention programs. Psychiatric or behavioural disorders that may interfere with adherence to the intervention. Ongoing use of medications known to significantly impair neuromuscular or cognitive function (e.g., strong muscle relaxants or sedatives). Inability to understand or follow basic instructions. Visual and/or hearing impairments that may hinder participation in the intervention or assessment.

Abbreviations: GDS: Global Deterioration Scale; MMSE: Mini-Mental State Examination.

**Table 2 healthcare-14-02467-t002:** Multicomponent Exercise Program Schedule.

Program	Weeks 1–2	Weeks 3–7	Weeks 8–12	Weeks 13–18
Warm-up/ Mobility	Dynamic mobility (e.g., spine, shoulders, wrists, hips, knees) and general stretching	Similar to week 1–2	Similar to week 1–2	Similar to week 1–2
Balance	Bipedal stance on stable surface: feet together, semi-tandem and tandem (bilateral). Bipedal stance on unstable surface: feet together. Eyes open.	Bipedal stance on stable surface: feet together, semi-tandem and tandem (bilateral). Bipedal stance on unstable surface: feet together and semi-tandem (bilateral). Eyes open/closed.	Bipedal stance on stable surface: semi-tandem, tandem and unipedal (bilateral). Bipedal stance on unstable surface: semi-tandem and tandem (bilateral). Eyes open/closed.	Bipedal stance on stable surface: tandem and unipedal (bilateral). Bipedal stance on unstable surface: tandem and unipedal (bilateral). Eyes open/closed.
Power	Knee extension (seated) and hip extension (bipedal stance). 2 sets × 10 reps (60% intensity/iRPE: 2–3, fRPE: 5–6)	Exercises from Week 1–2. 2 sets × 8 reps (65% intensity)./iRPE: 3–4, fRPE: 5–6)	Exercises from Week 1–2. 3 sets × 8 reps (70% intensity)/iRPE: 3–4, fRPE: 5–6)	Exercises from Week 1–2. 3 sets × 8 reps (70% intensity)./iRPE: 4–5, fRPE: 5–6)
Strength	- Lateral trunk inclinations. - Squat with shoulder raises. - Standing hip abduction. - Standing shoulder abduction. 2 sets × 10 reps (60% intensity/RPE 5–6)	- Lateral trunk inclinations. - Squat with shoulder raises. - Standing hip abduction. - Standing shoulder abduction. 2 sets × 10 reps (65% intensity/RPE 6–7).	- Squat with shoulder raises. - Standing hip abduction. - Standing shoulder abduction. 3 sets × 10 reps (70% intensity/RPE 7–8).	- Squat with shoulder raises. - Standing hip abduction. - Standing shoulder abduction. 3 sets × 8 reps (80% intensity/RPE 8–9).
Aerobics (endurance)	Varied gait patterns with speed/direction changes (e.g., military march, lateral/backward walking, lunges, jumps) (65% intensity/RPE 11)	Exercises from Week 1–2. (65–75% intensity/RPE 11–13)	Exercises from Week 1–2. (70–80% intensity/RPE 13–14)	Exercises from Week 1–2. (75–85% intensity/RPE 14–15)
Cool-down/Relaxation	Diaphragmatic breathing. Global stretching.	Exercises from Week 1–2.	Exercises from Week 1–2.	Exercises from Week 1–2.

Abbreviations: RPE: rating of perceived exertion; iRPE: initial rating of perceived exertion corresponding to the perceived exertion of the first repetition of the set; fRPE: final rating of perceived exertion corresponding to the perceived exertion at the end of the set.

**Table 3 healthcare-14-02467-t003:** Balance exercise progression.

Weeks	Type of Surface	Balance Exercise Program and Dose
Weeks 1–2	Stable surface	- Bipedal stance with feet together and eyes open. 3 × 30 s (total 1.5 min). Last set with hands crossing the shoulders. - Bipedal stance with feet together in semi-tandem position (bilateral) and eyes open. 3 × 30 s each side (total 3 min). Last set with hands crossing the shoulders. - Bipedal stance with feet together in tandem position (bilateral) and eyes open. 3 × 30 s each side (total 3 min). Last set with hands crossing the shoulders.
	Unstable surface	Bipedal stance with feet together and eyes open 3 × 30 s each side (total 3 min). Last set with hands crossing the shoulders.
Weeks 3–7	Stable surface	- Bipedal stance with feet together in semi-tandem position (bilateral) and eyes open. 3 × 30 s each side (total 3 min). Last set with hands crossing the shoulders. - Bipedal stance with feet together in tandem position (bilateral) and eyes open. 3 × 30 s each side (total 3 min). Last set with hands crossing the shoulders. - Bipedal stance with feet together and eyes closed. 2 × 30 s each side (total 1 min)
	Unstable surface	- Bipedal stance with feet together in semi-tandem position (bilateral) and eyes open. 3 × 30 s each side (total 3 min). Last set with hands crossing the shoulders. - Bipedal stance with feet together and eyes closed. 2 × 30 s each side (total 1 min). Last set with hands crossing the shoulders.
Weeks 8–12	Stable surface	- Bipedal stance with feet together in tandem position (bilateral) and eyes open. 2 × 30 s each side (total 2 min). Last set with hands crossing the shoulders. - Unipedal posture with eyes open. 2 × 30 s each side (total 2 min) - Bipedal stance with feet together in semi-tandem position (bilateral) and eyes closed. 2 × 30 s each side (total 2 min)
	Unstable surface	- Bipedal stance with feet together in semi-tandem position (bilateral) and eyes open. 2 × 30 s each side (total 2 min) Last set with hands crossing the shoulders. - Bipedal stance with feet together in tandem position (bilateral) and eyes open. 2 × 30 s each side (total 2 min). Last set with hands crossing the shoulders. - Bipedal stance with feet together in semi-tandem position (bilateral) and eyes closed. 2 × 30 s each side (total 2 min)
Weeks 13–18	Stable surface	- Bipedal stance with feet together in tandem position (bilateral) and eyes open. 2 × 30 s each side (total 2 min). Both sets with hands crossing the shoulders. - Bipedal stance with feet together in tandem position (bilateral) and eyes closed. 2 × 30 s each side (total 2 min) - Unipedal posture with eyes open. 2 × 30 s each side (total 2 min). Last set with hands crossing the shoulders. - Unipedal posture with eyes closed. 2 × 30 s each side (1 min)
	Unstable surface	- Bipedal stance with feet together in tandem position (bilateral) and eyes open. 2 × 30 s each side (total 2 min). Both sets with hands crossing the shoulders. - Bipedal stance with feet together in tandem position (bilateral) and eyes closed. 2 × 30 s each side (total 2 min) - Unipedal posture with eyes open. 2 × 30 s each side (total 2 min). Last set with hands crossing the shoulders.

Abbreviations: min: minutes; s: seconds.

**Table 4 healthcare-14-02467-t004:** Power training progression.

Weeks	Exercises	Volume	Intensity
Weeks 1–2	Seated knee extension Standing hip extension	2 sets × 10 reps	iRPE: 2–3, fRPE: 5–6
Weeks 3–7	Seated knee extension Standing hip extension	2 sets × 8 reps	iRPE: 3–4, fRPE: 5–6
Weeks 8–12	Seated knee extension Standing hip extension	3 sets × 8 reps	iRPE: 3–4, fRPE: 5–6
Weeks 13–18	Seated knee extension Standing hip extension	3 sets × 8 reps	iRPE: 4–5, fRPE: 5–6

Abbreviations: iRPE: initial rating of perceived exertion corresponding to the perceived exertion of the first repetition of the set; fRPE: final rating of perceived exertion corresponding to the perceived exertion at the end of the set.

**Table 5 healthcare-14-02467-t005:** Description of power exercises.

Exercise	Setup	Execution	Key Cues	Common Errors/Safety
Knee extension	Sit upright on a chair, elastic band looped around the working ankle and anchored under the chair leg; knee flexed ~90°.	Fast concentric knee extension to near full extension, 1 s isometric hold, controlled eccentric return (~2 s).	“Sit tall”; “extended fast, return slow”; “Knee tracks straight.”	Avoid hyperextension; reduce resistance if trunk moves; stop if knee pain > 2/10.
Standing hip extension	Stand facing a stable support (wall, bar, or chair) with feet hip-width apart. Elastic band looped around the working ankle and anchored to the opposite ankle or a low fixed point, with light pre-tension. Slight hip hinge with neutral pelvis, ribs down, core engaged; working knee slightly flexed.	Fast concentric hip extension moving the leg backward ~20–30° without lumbar sway, followed by a 1 s isometric hold. Controlled eccentric return to the starting position over ~2 s.	“Push the floor back with your heel.” “Move from the hip, not the low back.” “Keep the chest quiet and the core engaged.”	Lumbar extension or arching (reduce range, maintain rib control). Toe external rotation (maintain neutral alignment). Loss of balance or leg swinging (reduce band tension or use support). Avoid end-range lumbar extension; discontinue if sharp or radiating posterior hip pain occurs.

Abbreviation: s: seconds.

**Table 6 healthcare-14-02467-t006:** Prescription parameters in strength exercises.

Weeks	Exercises	Volume	Intensity
Weeks 1–2	Lateral trunk inclinations Squat with shoulder press Standing hip abduction Standing shoulder abduction (scapular plane, 30°)	2 sets × 10 reps	fRPE 5–6
Weeks 3–7	Lateral trunk inclinations Squat with shoulder press Standing hip abduction Standing shoulder abduction (scapular plane, 30°)	2 sets × 10 reps	fRPE 6–7
Weeks 8–12	Squat with shoulder press Standing hip abduction Standing shoulder abduction (scapular plane, 30°)	3 sets × 10 reps	fRPE 7–8
Weeks 13–18	Squat with shoulder press Standing hip abduction Standing shoulder abduction (scapular plane, 30°)	3 sets × 8 reps	fRPE 8–9

Abbreviations: fRPE: final rating of perceived exertion corresponding to the perceived exertion at the end of the set.

**Table 7 healthcare-14-02467-t007:** Description of strength exercises.

Exercise	Setup	Execution	Key Cues	Common Errors/Safety
Lateral trunk inclinations (side bends)	Stand tall with feet hip-width apart and knees slightly flexed. Hold the elastic band handle in the working hand; the opposite hand rests lightly on the pelvis. Core gently braced with ribs stacked over pelvic plane.	From an upright position, perform a controlled eccentric lateral trunk flexion by sliding the hand down the thigh, keeping shoulders level and avoiding rotation. Return concentrically to neutral using the contralateral trunk musculature.	“Grow tall, then tip—don’t twist.” “Keep the pelvis quiet; move through the ribs.”	Hip shift, lumbar extension, or trunk rotation. Perform only within a pain-free range and avoid end-range compression if spinal symptoms occur.
Squat with shoulder press	Stand with feet shoulder-width apart and toes slightly externally rotated. Anchor the elastic band under the feet and hold the handles at shoulder height with elbows slightly forward and trunk braced.	Perform a controlled eccentric squat to a comfortable depth. During the concentric phase, extend the hips and knees and simultaneously press the arms overhead to a soft lockout. Lower the arms back to shoulder level over ~2 s before the next repetition.	“Knees track, heels down; stand then reach tall.” “Keep ribs down during the press.”	Knee valgus, heel lift, lumbar extension during the press, or initiating the press before full LL extension. Maintain a pain-free shoulder range and discontinue if lumbar extension is required.
Standing hip abduction (straight-leg)	Stand facing a stable support. Elastic band looped around both ankles. Feet parallel, pelvis neutral, knees slightly flexed, trunk upright.	Move the working leg laterally ~20–30° without pelvic elevation or trunk lean. Hold for 1 s at end range, then return to the starting position over ~2 s under control. Repeat and switch sides.	“Engage the core; slide the leg sideways.” “Keep toes and kneecap facing forward.”	Trunk lean, pelvic hike, toe external rotation, or snapping at the hip. Avoid lateral trunk compensation and stop if sharp lateral hip pain occurs.
Standing shoulder abduction in the scapular plane	Stand upright with neutral spine. Hold elastic band handles with arms positioned ~30° anterior to the frontal plane (scapular plane), thumbs slightly up.	Raise both arms in the scapular plane to approximately 90° of shoulder elevation without shrugging. Hold for 1 s, then lower the arms over ~2 s under control.	“Ribs down, neck long.” “Lift in the scapular plane—don’t shrug.”	Shoulder shrugging, rib flare, internal rotation of the arms, or lifting beyond symptom-free range. Maintain scapular plane positioning and stop if impingement pain occurs.

**Table 8 healthcare-14-02467-t008:** Description of aerobic exercises.

Phase	Main Aerobic Tasks	Duration	Intensity	Progression Criteria
Weeks 1–2	Forward/backward walking, side stepping, marching tasks	10 min.	65% HRmax. Borg RPE 11	Familiarization with movement patterns
Weeks 3–7	Multidirectional gait, tempo changes, coordinates arm-leg tasks	10 min.	65–75% HRmax. Borg RPE 11–13	Increased movement complexity and tempo
Weeks 8–12	Accelerations/decelerations, obstacle negotiation, dance-based sequences	10 min.	70–80% HRmax. Borg RPE 13–14	Reduced external support and increased coordination demands
Weeks 13–18	Dual-task gait, reactive stepping, complex gait sequences	10 min.	75–85% HRmax. Borg RPE 14–15	Increased cognitive and motor complexity

Abbreviations: min: minutes; HRmax: maximum heart rate; RPE: rating of perceived exertion.

**Table 9 healthcare-14-02467-t009:** Description of the PSY intervention sessions.

Session	Core Focus	Key Contents/Techniques	Home Practice
1	Understanding emotions	Components of emotional experience (thoughts, behaviours, and physiological sensations) and their interaction.	Emotional experience logs
2	Emotional awareness	Analysis of learned emotional responses will be discussed through four key principles: (1) individuals learn from past experiences, approaching what feels pleasant and avoiding what feels unpleasant; (2) behavioural patterns often develop to prevent exposure to potential discomfort; (3) some behaviours initially used to manage intense emotions become habitual over time (e.g., avoiding eye contact); and (4) although emotion-driven behaviours may appear adaptive, repeated reliance on them can reinforce maladaptive cycles that become insensitive to context.	Practice of experimental exercises
3	Understanding thoughts	Identification of emotion-related thoughts; cognitive distortions; cognitive reappraisal and cognitive defusion techniques.	Continued cognitive practice
4	Understanding behaviors	Adaptive vs. maladaptive behaviours; emotional avoidance and safety behaviours; planning of alternative responses.	Practice and alternative behaviors
5	Perspective-taking and acceptance	Self-observation from an integrated perspective; acceptance and compassion-focused exercises.	Perspective-taking practice
6	Self-acceptance and self-compassion	Four A’s model: (1) Attention, (2) Appreciation, (3) Affection, and (4) Acceptance; compassionate-self exercise; program summary	Continue self-compassion practice

